### Study design

This study is a prospective single blinded randomized, multicenter, multimodal (clinical and biomechanical) clinical trial.

### Participants

We will examine 60 patients undergoing isolated MPFL reconstruction due to patella dislocation. The patients will be randomly assigned to the procedure (static reconstruction technique according to Schöttle et al. [20] or dynamic reconstruction technique according to Becher et al. [29]) using an a priori generated list of codes assigned in five blocks of six codes per center generated with a block randomization generator (www.sealedenvelope.com). Patients and the staff collecting questionnaires or biomechanical data will be blinded to the surgical procedure.

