## Clinical trial protocol

Data of the patients will be collected pre- and postoperatively, and all patients will be in contact with the study staff for 2 years (Fig. 2). All patients fulfilling the inclusion criteria will be enrolled consecutively, thus avoiding selection bias. Participants will be followed up for 2 years with a total of five follow-ups at 6 weeks, 12 weeks, 6 months, 12 months and 24 months. Preoperative magnetic resonance imaging (MRI), upright radiographs, surgical reports and patient files will be evaluated. Patients who fulfil the inclusion criteria but refuse participation will be documented in a separate screening log.

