#### Sample size calculation

We based our sample size calculation on the primary outcome, the Kujala score. To date, no high-quality study (randomized trial) on the difference in change in Kujala score between dynamic and static MPFL reconstruction is available. However, in a prospective randomized control trial, Kang et al. [56] compared two different tensioning techniques for static MPFL reconstruction. They reported an effect size of 7.8 for the improvement in the Kujala score for both groups and a group difference in change in Kujala score of 1.9. Based on biomechanical considerations, we expect a larger improvement in patients stabilized using the dynamic MPFL reconstruction. Assuming a 3.8-point improvement in the Kujala score in patients with dynamic MPFL reconstruction compared to patients with static MPFL reconstruction, 54 patients (27 per group) are required to detect a significant difference in change in Kujala score between the two groups with 80% power at a significance level of 5%. We expect a dropout rate of about 10%, and will thus we will target a study cohort of 60 patients (30 per group).

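### One fixed, published block length of six per centre could let anyone who knows a centre's earlier allocations predict up to a quarter of them with certainty, so consecutive enrolment alone does not rule out selection bias.

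*Protocol article*

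**What the plan says.** Under Participants, the protocol article assigns patients to the static or dynamic technique "using an a priori generated list of codes assigned in five blocks of six codes per center", produced with an online block generator. The same section states: "Patients and the staff collecting questionnaires or biomechanical data will be blinded to the surgical procedure". Surgeons are not listed there. The section on the two techniques describes operations that the operator cannot confuse: a harvested graft fixed with three suture anchors, against a distally detached, redirected tendon fixed to the patella with one.

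Under Clinical trial protocol, the article says: "All patients fulfilling the inclusion criteria will be enrolled consecutively, thus avoiding selection bias". It also plans a screening log of eligible patients who refuse.

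The total is 60, with 30 per group (Sample size calculation). Study design calls the trial multicentre without giving the number of centres. The article does not describe who holds the list, who enrols, or when a code is released.

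**The concern.** A block of one known length has a predictable end. Once one arm has used its share, the remaining codes are fixed, and the last code of every block always is. Here the length is published, the lists are separate for each centre, and the surgeons necessarily learn which technique each of their own patients received.

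Consecutive enrolment governs who is approached. It does not stop an eligibility judgement, or the timing of enrolment, from depending on an allocation that someone can foresee. Some judgement does exist: the inclusion criteria require that no further static risk factor be clinically relevant.

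The trial is small, its primary outcome is patient-reported, and the sample size rests on a 3.8-point difference. The investigators also state that they expect the dynamic technique to do better. Selection that enters during recruitment cannot be reliably removed in the analysis.

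**Working it through.** **Inputs.** Block length 6, five blocks per centre (Participants). Total 60, 30 per group, 54 evaluable, about 10% dropout, assumed difference 3.8 points (Sample size calculation). The 3:3 split within a block is inferred from the equal groups. The number of centres is not stated.

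**The plan's own figure.** 54 / (1 - 0.10) = 60, as stated. Codes per centre: 5 x 6 = 30. 60 / 30 = 2, so the list is exactly used up if there are two centres.

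**Certain allocations.** A 3:3 block has 20 equally likely orders. The codes that can be known in advance are those in the final run of one arm.
- Final run of 1: 12 of 20 (0.6)
- Final run of 2: 6 of 20 (0.3)
- Final run of 3: 2 of 20 (0.1)

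Mean = 0.6 x 1 + 0.3 x 2 + 0.1 x 3 = 1.5 of 6 = 25%. Ten full blocks give 10 x 1.5 = 15 of 60. Blocks left incomplete would lower this.

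**Guessing the arm that is behind.** In each block three steps bring the arms back towards balance, and all three are guessed correctly. Steps taken from a tie are guessed correctly half the time. Expected ties before a step: 1 at the start + 0.6 after two codes + 0.6 after four = 2.2. Correct guesses = 3 + 2.2 / 2 = 4.1 of 6 = 68.3%, against 50% by chance.

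**Effect of varying the length.** By simulation over 30 allocations, for an observer who knows the possible lengths but not the actual ones, the share of certain codes is:

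| Lengths | Certain |
|---|---|
| 6 only | 25.0% |
| 4, 6 | 5.6% |
| 2, 4, 6 | 3.9% |
| 4, 6, 8 | 2.3% |

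Varying the length does not remove the advantage of guessing, because that needs only the running tally. Per block, the correct-guess rates are 70.8%, 68.3% and 66.6% for lengths 4, 6 and 8. Used equally often, these give (4 x 0.708 + 6 x 0.683 + 8 x 0.666) / 18 = about 68%.

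**Possible shift in the result (assumed values).** If k of 30 patients in one arm are replaced by patients whose change score differs by d points, the arm mean moves by k x d / 30. For k = 4 and d = 5 this is 0.7 points; for k = 4 and d = 10 it is 1.3; for k = 3 and d = 10 it is 1.0.

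**Code supply.** With two centres, any split other than 30/30 exhausts one list before 60 are enrolled: probability 0.90 at equal recruitment rates and 0.97 at an expected 60:40 split. With three centres (90 codes) one centre must exceed 30 patients: 0.007 at equal shares, 0.45 at 50:25:25, 0.93 at 60:20:20. With four equal centres it is practically zero.

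**The case against.** Fixed blocks within centre are a common choice and contradict nothing in the article. A reader might infer that the surgeons use the list and that a quarter of allocations will in fact be foreseen. The article supports neither. It does not say that surgeons enrol patients or hold the list, and concealment may well be set out in the full protocol, which a condensed article need not repeat. With several surgeons per centre, or an enroller who does not operate, fewer codes could be foreseen. This stands: 25% and 68% are upper bounds.

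A reader might also infer that codes will run out whenever recruitment is uneven. That follows only with exactly two centres. Even then the faster centre could stop at 30 and the total of 60 could still be reached. This too stands.

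Eligibility is less open than it might look. Asymptomatic dysplasia is defined by stability over a range of flexion, and most exclusions have numeric limits. The screening log is a partial safeguard, although it covers refusals and not deferrals or adverse eligibility judgements. Nor could a few steered patients plausibly produce the whole 3.8 points: three patients would each have to differ by 3.8 x 30 / 3 = 38 points.

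None of this rescues the causal claim about consecutive enrolment. Hiding individual codes does not prevent someone who knows the earlier allocations from working out the end of a block of known length.

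**Conclusion.** The point holds as a weakness in a stated method and an overstatement in the text. One fixed, disclosed length of six per centre, with operating surgeons who cannot be blinded, leaves up to 25% of allocations open to certain prediction (at most about 15 of 60 on average) and up to 68% to a correct guess. This assumes 3:3 blocks and a person involved in enrolment who knows all earlier allocations at that centre; with the length known, the block boundaries follow by counting. The documents do not show that such a person exists or that any allocation has been steered. Under the assumed values above, a bias would be of the order of one point or less, against a target of 3.8.

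The code supply is a secondary matter. It bites if there are only two centres, or if one of several dominates recruitment; with three or more centres of similar size it rarely matters.

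**What to change.** 1. For codes not yet used, starting once the current block at each centre is complete, generate the centre lists with randomly varying, undisclosed block lengths, for example 4, 6 and 8. Leave out blocks of two: if the length becomes known, the second code of each is certain (50%, against 33%, 25% and 20% for lengths 4, 6 and 8).
2. Delete the clause that credits consecutive enrolment with avoiding selection bias, or limit it to selection in who is approached.
3. Give the new lists reserve codes, so that unequal recruitment cannot exhaust one if there are only two centres or one centre dominates.

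**Cost.** Generating new lists and a short text change. The downside is a slight possible imbalance between arms at the end of each list. The change cannot undo the published length for codes already used. It removes most of the certainty but not the guessing advantage, which only limiting the enroller's knowledge of earlier allocations can reduce. If recruitment is nearly complete, only the text change is worthwhile.

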#### Inclusion criteria

Inclusion criteria are: isolated MPFL reconstruction due to patella instability in patients with closed growth plates; patella dislocation; Patella-Instability-Severity (PIS) score [42] ≤ 3 with concomitant flake fracture; PIS score ≤ 4 with clinical asymptomatic trochlea dysplasia (patella stability between 30 and 60° knee flexion); and no other clinically relevant static risk factors as patella alta or increased tibial tuberosity trochlear groove distance.

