**Methods:**

This study is a prospective, single blinded, randomized, multicenter, multimodal (clinical and biomechanical) clinical trial. Patients with recurrent patella dislocation requiring isolated MPFL reconstruction will be recruited and randomized to the dynamic or static reconstruction technique. Participants will be followed up for 2 years with a total of five follow-ups. Preoperative magnetic resonance imaging, upright radiographs, surgical reports and patient records will be evaluated, and clinical and functional outcomes will be measured. Patient-reported knee function and anterior knee pain as assessed with the Kujala score will serve as primary outcome. For biomechanical outcome, pre- and postoperative evaluations will be performed to assess isokinetic muscle strength, gait asymmetry, joint kinematics and kinetics, and timing of muscle activity.

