The leading surgical strategy is to stabilize the patella through a reconstruction of the insufficient or disrupted soft tissue of the MPFL. This is necessary in recurrent patella dislocations and in particular cases of first patella dislocations such as patients with severe anatomical risk factors [15]. The anatomical risk factors should be corrected as well because these patients have an increased rate of revision surgeries, re-dislocations and persistent joint instability compared to those without anatomical risk factors [16]. Moreover, a prolonged time from dislocation to surgery appears to be associated with increased risk of re-dislocations [17]. To date, experts disagree regarding the treatment of complex patella instability [18]. In MPFL reconstruction, a graft (harvested autologous tendon or allograft) intended to stabilize the patella is placed using tunnels, screws, and/or anchors. While the use of interference screws versus suture anchors for isolated MPFL reconstruction has been shown to have similar clinical outcomes, the use of screws was associated with slightly higher complication rates [19]. One established procedure is the static MPFL reconstruction according to Schöttle et al. [20] (Fig. 1), who use the autologous gracilis tendon to stabilize the patella with a static reattachment to the femur. Despite good long-term outcomes of the static MPFL technique [16, 21–23] for up to 4 years, there remains a risk of malpositioning or over-tensioning the graft [24]. While too low graft tension leads to recurrent instability and failure, too high graft tension can lead to persistent knee pain and result in higher patellofemoral pressure, which may ultimately lead to patellofemoral joint degeneration and osteoarthritis [22, 25–27]. Over-tensioning is one of the most challenging complications—even in clinically adequately placed MPFL reconstructions—as the graft used for reconstruction is isometric, whereas the anatomical MPFL is a mostly dynamic structure [28] being tight in extension and early flexion and nearly isometric beyond 30° of flexion [24].

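### The protocol does not say consistently whether recurrent dislocation is required, or how the inclusion items combine

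*Protocol article*

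**What the plan says.** The Methods part of the abstract states: "Patients with recurrent patella dislocation requiring isolated MPFL reconstruction will be recruited and randomized to the dynamic or static reconstruction technique".

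The Participants paragraph states: "We will examine 60 patients undergoing isolated MPFL reconstruction due to patella dislocation". It does not mention recurrence.

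The inclusion list opens with "isolated MPFL reconstruction due to patella instability in patients with closed growth plates". It continues with "patella dislocation; Patella-Instability-Severity (PIS) score [42] ≤ 3 with concomitant flake fracture; PIS score ≤ 4 with clinical asymptomatic trochlea dysplasia" and closes with "and no other clinically relevant static risk factors as patella alta or increased tibial tuberosity trochlear groove distance". The items are separated by semicolons, and *or* never links the two PIS items.

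The exclusion list covers combined procedures, arthritis, malalignment, ligament instability, other disease and age. It says nothing about the number of previous dislocations.

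The section headed Clinical trial protocol says that all patients who meet the inclusion criteria are enrolled consecutively, and that eligible patients who decline go into a screening log.

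**The concern.** There are two separate defects in the same text.

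First, a patient with a single dislocation is outside the population in the abstract but is not turned away by the Participants paragraph, the inclusion list or the exclusion list. The distinction is one the authors draw themselves. The Background says of soft-tissue reconstruction: "This is necessary in recurrent patella dislocations and in particular cases of first patella dislocations". That sentence describes surgical practice in general and does not define this trial's population, but it shows that the two groups are not interchangeable in the authors' own account.

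Second, a centre cannot tell from the inclusion list which items are joint requirements and which are alternative routes in.

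The stake is practical. Consecutive enrolment is offered as the safeguard against selection, and the screening log counts eligible refusals. Both depend on criteria that every centre reads in the same way. If they do not, the enrolled cohort is a mixture set by local interpretation, and the report would have difficulty saying to whom its estimate applies.

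**Working it through.** No figure in the protocol depends on this point, so the check compares the passages and tests the logic of the list.

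**Step 1: recurrence.**

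| Place | Requirement | First dislocation |
|---|---|---|
| Abstract, Methods | recurrent dislocation | outside |
| Participants | dislocation | inside |
| Inclusion criteria | instability and dislocation | not barred |
| Exclusion criteria | silent | not barred |

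The abstract conflicts with the other three places on this point, and no text resolves the conflict.

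**Step 2: how the items combine.** Take patients who have dislocated and meet the remaining items (closed growth plates, no other relevant static risk factor). Cross flake fracture (yes/no), asymptomatic dysplasia (yes/no) and PIS score (2, 3, 4): 2 × 2 × 3 = 12 combinations.

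- *Reading A, both PIS items required.* Flake fracture and dysplasia must both be present, with PIS ≤ 3: 1 × 1 × 2 = 2 combinations qualify. The ≤ 4 limit does no work, because ≤ 3 already applies.
- *Reading B, either PIS item suffices.* Dysplasia with PIS ≤ 4, with or without flake fracture: 2 × 3 = 6. Flake fracture without dysplasia, PIS ≤ 3: 2. Total 6 + 2 = 8 combinations qualify.
- *Reading C, dislocation is itself a sufficient indication alongside the two PIS items.* All 12 qualify, and the PIS limits exclude nobody who has dislocated.

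These counts show the logic only. They are not prevalences.

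**Step 3: two example patients.**

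| Patient | Abstract | Participants | A | B | C |
|---|---|---|---|---|---|
| First dislocation, flake fracture, no dysplasia, PIS 3 | out | in | out | in | in |
| Recurrent dislocation, neither feature, PIS 2 | in | in | out | out | in |

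The second patient fits the abstract and the Participants paragraph, yet is eligible under the inclusion list only on Reading C. Settling the recurrence question alone would therefore not settle eligibility.

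**Step 4: what randomisation protects.** Codes are generated per centre in five blocks of six, that is 5 × 6 = 30 codes per centre. If one centre admits first dislocations and another does not, both arms within each centre draw on the same mix in expectation. The comparison is not biased by this, although chance imbalance in a small trial remains possible.

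**The case against.** The strongest reply is that the inclusion list is ordinary loose prose. The exclusion list has the same form, a semicolon series closed by *and*, and its items are plainly alternatives, since any one of them excludes. The closing *and* in the inclusion list therefore proves little about joint requirement. The differing PIS limits also point to alternatives. This stands. A reader might infer that the protocol requires flake fracture and dysplasia together, but the documents do not support that as the settled meaning. What remains is ambiguity: other items in the same list, such as closed growth plates and absence of other static risk factors, clearly are joint requirements, so the list mixes the two kinds without marking them.

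A second reply is that the report can describe its patients anyway. Medical history and preoperative imaging are collected, and patient characteristics are tabulated by group. This softens the harm but does not remove it. A table describes who was enrolled; it does not make enrolment uniform or say who was meant to be eligible.

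A third reply is that covariate adjustment is commonly left to the analysis plan, which is not shown. That is fair. Adjustment is offered here as a sensible companion to the wording change and is not charged as an omission.

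**Conclusion.** The contradiction over recurrence is certain on the text, and the ambiguity over how the inclusion items combine is real. Together they affect how uniformly centres enrol and how the result can be generalised. They do not undermine the comparison between arms, given randomisation blocked within centre.

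A reader might go on to infer a loss of power, on the argument that first or flake-fracture dislocations start from a lower Kujala score and widen the spread of change. The documents do not support a figure for this. They give no share of such patients, no score difference and no standard deviation behind the sample size, and they nowhere equate flake fracture with first dislocation. The argument also cannot be combined with the joint reading of the two PIS items: if every patient had a flake fracture, there would be no flake-fracture subgroup to add variance. No quantified loss is claimed.

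The conclusion assumes only that centres work from text like that printed here. A fuller protocol that settles both questions would reduce this to an error of reporting.

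**What to change.** 1. Reconcile the abstract, the Participants paragraph and the inclusion list so that all three name the same population, either recurrent only or first and recurrent. Which one is a clinical decision for the sponsor.
2. Rewrite the inclusion list so that joint requirements and alternatives are marked explicitly, and state whether a patient with neither flake fracture nor dysplasia is eligible.
3. If first and recurrent dislocations are both eligible, record that status at baseline. Adjust the primary comparison for it and for the preoperative Kujala score, instead of relying only on the difference in means that the Statistical analysis section describes, with the relation to baseline examined in addition.

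Items 1 and 2 are a wording amendment. Item 3 should need little new data: Table 1 already schedules the Kujala score and medical history at hospitalisation. Two covariates cost about two degrees of freedom: with 60 patients in two arms, residual degrees of freedom go from 60 − 2 = 58 to 58 − 2 = 56.

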#### Exclusion criteria

Exclusion criteria are: combined procedures with trochleoplasty (trochlea dysplasia Type C or D according to Dejour et al. [43] with clinical instability between 30 and 60° of knee flexion); combined procedures with cartilage transplantation; high grade patellofemoral arthritis (Kellgren Lawrence [44] score ≥ 3); combined procedures with femoral or tibial osteotomy; clinically eminent valgus axis (> 15° valgus); femoral internal rotation > 20°; tibial external rotation > 40°; instability of the cruciate or collateral ligaments; known significant musculoskeletal disease or cognitive impairment; and patient age < 14 years.

#### Ethical considerations

The study protocol was approved by the regional ethics board (Ethics Committee Northwest Switzerland EKNZ 2020-02701) and registered at clinicaltrials.gov (NCT04849130). Written informed consent will be obtained from all participants prior to participation.

## Clinical trial protocol

Data of the patients will be collected pre- and postoperatively, and all patients will be in contact with the study staff for 2 years (Fig. 2). All patients fulfilling the inclusion criteria will be enrolled consecutively, thus avoiding selection bias. Participants will be followed up for 2 years with a total of five follow-ups at 6 weeks, 12 weeks, 6 months, 12 months and 24 months. Preoperative magnetic resonance imaging (MRI), upright radiographs, surgical reports and patient files will be evaluated. Patients who fulfil the inclusion criteria but refuse participation will be documented in a separate screening log.

